**MODIFICATION HISTOY:**

| Version(Date) | Authors | Action/modification |
| --- | --- | --- |
| V1 (2022-02-21) | [name], [name] | Created this statistical analysis plan (SAP) |
| V2 (2022-10-12) | [name], [name] | Revised SAP based on all coauthors' comments and the analyses will be conducted after this version until January 2023. |
| V3 (2023-07-07) | [name], [name] | Revised SAP based on comments from external reviewers |

**STUDY OBJECTIVES**

To investigate the long-term risk of arrhythmias in patients with inflammatory bowel disease (IBD).

**HYPOTHESIS**

Because of the present knowledge about the role of systemic inflammation in the development of cardiovascular diseases, we hypothesize that patients with IBD are at an increased risk of overall arrhythmias and specific types of arrhythmias, including atrial fibrillation/flutter, bradyarrhythmias, other supraventricular arrhythmias, and ventricular arrhythmias/cardiac arrest.

**METHODS**

**Data source, study design and participants**

This cohort will be based on the nationwide histopathology cohort, Epidemiology Strengthened by histoPathology Reports in Sweden (ESPRESSO) [1], and several healthcare registers in Sweden. ESPRESSO includes histopathology data from all 28 pathology departments in Sweden recorded between 1969 to 2019 (changed into 2017 in the revision), including date on biopsy, topography, and morphology (recorded by the Swedish version of the Systematized Nomenclature of Medicine (SNOMED) system) [1].

Patients with IBD will be identified as those with at least one International Classification of Disease (ICD) code for IBD in the Swedish National Patient Register (NPR) and one biopsy record indicating IBD in the ESPRESSO (see below **Table 1** for ICD codes, SNOMED codes, and definitions of IBD subtypes)[2]. Date of IBD diagnosis (i.e., index date) will be defined as the second of receiving first ICD or first biopsy codes.

The Montreal classification will be used to define Crohn's disease (CD) location, ulcerative colitis (UC) extent, and perianal disease modifier [3]. CD location includes ileal (L1)/ileocolonic (L3)/unknown (LX) or colonic (L2). UC extent includes proctitis (E1)/left-sided colitis (E2), extensive colitis (E3) or extent not defined (EX) (see below **Table 2** for ICD codes).

**General population reference individuals and sibling comparators**

For each patient with IBD, we will randomly select up to five reference individuals from the Total Population Register (matched by birth year, sex, county of residence, and calendar year)[4]. Full siblings to patients with IBD will be identified through the Multi-Generation Register [5]. The reference individuals and full siblings have to be alive, living in Sweden, and free of IBD and arrhythmia when being selected (i.e., index date).

**Follow-up and ascertainment of outcome**

Individuals with previous arrhythmia (see below **Table 3** for ICD codes) before index date will be excluded. Follow-up will start at index date until incident diagnosis of arrhythmias, emigration, death, or December 31, 2019, whichever occurs first. Reference individuals or IBD-free full siblings will also be censored when receiving a diagnosis of IBD during follow-up. Individuals with an incident arrhythmia will be identified from the NPR, considering both primary and secondary diagnosis. The primary outcome is the incidence of overall arrhythmias. The secondary outcomes are the incidences of atrial fibrillation/flutter, bradyarrhythmias, other supraventricular arrhythmias, and ventricular arrhythmias/cardiac arrest. If one individual is diagnosed with more than one of the secondary outcomes, this individual will contribute to each outcome with the respective diagnosis date.

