**STATISTICAL ANALYSES**

We will report incidence rate (IR) and IR difference, together with 95% confidence intervals (CIs) for all outcomes. To estimate the average and temporal patterns of hazard ratios (HRs) and 95% CIs for incident arrhythmias in relation to IBD, flexible parametric survival models will be applied to allow the effect of IBD to vary over time (time-varying effect)[8]. Time since index date will be used as the underlying time scale. Standardized cumulative incidence and its differences of arrhythmia will be estimated. We will report the cumulative incidence difference at 1 year, 5 years, 10 years, and 25 years after index date. In the population matched cohort, we will condition the analyses on the matching variables (birth year, sex, county of residence, and calendar year) in model 1, and additionally adjust for country of birth, educational attainment, number of healthcare visits, ischemic heart disease, heart failure, stroke, hypertension, diabetes, obesity, dyslipidemia, chronic kidney disease, and COPD in model 2.

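### Comparators must be arrhythmia-free at the index date, but patients are excluded only for arrhythmia before it, so same-day codes can inflate early estimates in IBD

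*SAP*

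**What the plan says.** All references are to the SAP.

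- **Exclusion and start of risk time** (Follow-up and ascertainment of outcome). For all individuals, prior arrhythmia is handled as "before index date will be excluded. Follow-up will start at index date until incident diagnosis of arrhythmias".
- **Comparators** (General population reference individuals and sibling comparators). References and siblings must, in addition, be "free of IBD and arrhythmia when being selected (i.e., index date". There is no matching condition for patients.
- **Index date of patients** (Data source, study design and participants). It "will be defined as the second of receiving first ICD or first biopsy codes". It is therefore the later of the first IBD code in the National Patient Register (NPR) and the first IBD biopsy.
- **Outcome source** (Follow-up and ascertainment of outcome). "Individuals with an incident arrhythmia will be identified from the NPR, considering both primary and secondary diagnosis".
- **Estimates** (Statistical analyses). Incidence rates, a flexible parametric model with a time-varying IBD effect, and cumulative incidence: "We will report the cumulative incidence difference at 1 year, 5 years, 10 years, and 25 years after index date". For the model, "Time since index date will be used as the underlying time scale". None of these has a lag.
- **Early events** (Subgroup and sensitivity analyses). The fourth sensitivity analysis repeats the main analysis without people whose arrhythmia was recorded in the first 1 or 3 years.

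The SAP does not say how an arrhythmia dated on the index date, or a follow-up time of zero, is handled.

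**The concern.** For a patient, the index date is always a care event. If it is the date of an NPR contact, a long-standing arrhythmia may be listed there for the first time as a secondary diagnosis. A comparator is assigned the date and needs no contact on it, and the SAP requires the comparator to be free of arrhythmia at that date.

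A same-day code is thus screened out on one side and can be counted on the other. Any resulting bias favours the study hypothesis of higher risk in IBD. It would fall on the earliest part of follow-up, which is where the 1-year cumulative incidence difference and the start of the HR curve are read.

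**Working it through.** **The rules side by side**

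| Arrhythmia code dated | Patient | Reference or sibling |
|---|---|---|
| Before the index date | Excluded | Excluded |
| On the index date | Not excluded; at risk from that day | Not eligible for selection |
| After the index date | Event | Event |

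The middle row is the inconsistency, and it follows from the wording alone.

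**Size, for illustration**

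The SAP gives no arrhythmia rate, event count or sample size, so there is no planned figure to reproduce. Both inputs below are assumptions:

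- *r* = comparator arrhythmia rate, taken as constant: 5 per 1,000 person-years
- *q* = share of patients with an arrhythmia coded on day 0: 0.05%, 0.1% or 0.2%

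Comparators have no day-0 events, because they are selected free of arrhythmia. With no true effect:

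- Comparator risk to year *T*: F0 = 1 − exp(−*rT*)
- Patient risk: F1 = *q* + (1 − *q*) × F0
- Difference: F1 − F0 = *q* × exp(−*rT*)

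At 1 year, F0 = 1 − exp(−0.005) = 0.49875%. For *q* = 0.1%, the difference is 0.1% × 0.9950 = 0.0995 percentage points and the risk ratio is (0.49875 + 0.0995)/0.49875 = 1.20. For *q* = 0.05% and 0.2% the differences are 0.050 and 0.199 points, and the risk ratios 1.10 and 1.40.

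At the later planned time points, with *q* = 0.1%:

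| Years | F0 | Difference (points) | Risk ratio |
|---|---|---|---|
| 1 | 0.499% | 0.100 | 1.20 |
| 5 | 2.469% | 0.098 | 1.04 |
| 10 | 4.877% | 0.095 | 1.02 |
| 25 | 11.750% | 0.088 | 1.01 |

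The absolute shift stays close to *q* throughout. It matters at 1 year because the background risk is then small.

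**Other assumed rates**

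The incidence rate ratio (IRR) is events over person-time in each group, with the same constant hazards. With no true effect and *q* = 0.1%:

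| Rate per 1,000 person-years | IRR, first year | IRR, 25 years |
|---|---|---|
| 3 | 1.33 | 1.014 |
| 6 | 1.17 | 1.007 |
| 10 | 1.10 | 1.005 |

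With an assumed true HR of 1.2 and 6 per 1,000:

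| *q* | 1-year difference (points) | IRR, first year | IRR, 10 years | IRR, 25 years |
|---|---|---|---|---|
| 0 | 0.12 | 1.20 | 1.200 | 1.200 |
| 0.1% | 0.22 | 1.37 | 1.217 | 1.207 |
| 0.5% | 0.62 | 2.04 | 1.287 | 1.237 |

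The row *q* = 0 is the result once day-0 codes are treated as prevalent.

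**Does the planned sensitivity analysis settle it?** It removes every day-0 event, but it also removes genuine events in the first 1 or 3 years. It therefore cannot supply a corrected 1-year difference.

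**The case against.** **The SAP never says that day-0 codes count.** A reader might infer that they are events by rule. The text supports less: it speaks of previous arrhythmia before the index date and of incident diagnoses after follow-up starts, and is silent on the day itself. This stands, so the claim is that such codes can count.

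**The index date need not be an NPR contact.** If the ICD code came first, the index date is a biopsy record, whereas outcomes come from the NPR. That patient has also had an earlier NPR contact, where a known arrhythmia could have been coded and led to exclusion. This stands. The mechanism applies mainly when the biopsy came first or both fell on the same day.

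**Zero-time events may not enter the model.** A reader might infer that the main HR is inflated. A model on log time cannot use a survival time of zero without an offset, and the SAP states none. If the software drops these patients, the HR is as if they had been excluded. The same holds for the 1-year difference if it is derived from that model, which the SAP does not specify. This stands, but it does not close the gap: incidence rates computed outside the model could still count the events, and the handling would rest on unstated defaults in three software packages.

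**The assumed *q* is high relative to background.** The chance of an event on a given day is 0.005/365.25 = 1.37 per 100,000, so *q* = 0.1% is about 73 times that. Day-0 coding at a care contact is not a background process, so the comparison does not refute the assumption. The true *q* is nevertheless unknown.

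**The objective is long-term risk, and early events are already tested.** Both are true and limit the point's importance. Neither corrects the 1-year difference, which the SAP plans to report.

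**Conclusion.** The point holds as an inconsistency between two stated rules that can bias early estimates towards higher risk in IBD. With 5 per 1,000 person-years, no true effect and *q* = 0.05% to 0.2%, the 1-year difference moves by about 0.05 to 0.2 percentage points and the 1-year risk ratio by a factor of 1.10 to 1.40. These sizes rest on assumed inputs, constant hazards and same-day codes being retained as events.

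A reader might go further and infer that a long-term excess risk in IBD could be produced by this rule. The figures do not support that: at *q* = 0.1% with no true effect, the 25-year IRR is 1.005 to 1.014 across the assumed rates. Nor does the SAP show that same-day codes were in fact counted. The rule should be settled, because the ambiguity is one-sided and the remedy is simple.

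**What to change.** In Follow-up and ascertainment of outcome:

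1. Exclude arrhythmia recorded *on or before* the index date, for patients, references and siblings alike.
2. Start risk time on the day after the index date in all three groups. No arrhythmia event then has zero follow-up time.
3. Report the number excluded for day-0 codes in each group. This replaces the assumed *q* with an observed figure and shows whether the issue mattered.

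The exclusion should not extend to every arrhythmia recorded in a hospital stay that spans the index date. That could remove true post-index events, mainly in patients.

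The cost is a change of wording and a small program change. A few true day-0 events are lost, mainly in patients, since comparators must already be arrhythmia-free at that date. The modification history indicates that analyses were scheduled after version 2 and that version 3 responds to external review, so the main estimates would probably have to be re-run.

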**Covariates**

We will retrieve information on country of birth (available from 1947 onward, Nordic or others) from the Total Population Register [4] and educational attainment (available from 1990 onward; 4 groups: 0-9 y, 10-12 y, ≥13 y, and “missing”, a proxy for socioeconomic status) from the Swedish Longitudinal Integrated Database for Health Insurance and Labour Market Studies [6]. As a proxy for regular healthcare seeking behavior, number of healthcare visits will be retrieved from the NPR (4 groups: 0, 1, 2-3, and ≥4,) which is defined as the number of specialized (non-primary care) outpatient visits or hospitalizations between 2 years and 6 months before index date. Data on cardiovascular related comorbidities preceding index date will be collected from the NPR, including ischemic heart disease, heart failure, stroke, hypertension, diabetes, obesity dyslipidemia, chronic kidney disease, and chronic obstructive pulmonary disease (COPD, only if patient diagnosed ≥40 year) (see below **Table 4** for ICD codes). Information regarding use of the cardiovascular related medications preceding index date will be collected from the Prescribed Drug Register [7] (data available from July 2005 onward): aspirin, non-aspirin anti-platelet medications, statins, non-statin lipid lowering medications, anticoagulation medications, antidiabetic medications, and antihypertensive agents (see below **Table 5** for the Anatomical Therapeutic Chemical codes).

**STATISTICAL ANALYSES**

We will report incidence rate (IR) and IR difference, together with 95% confidence intervals (CIs) for all outcomes. To estimate the average and temporal patterns of hazard ratios (HRs) and 95% CIs for incident arrhythmias in relation to IBD, flexible parametric survival models will be applied to allow the effect of IBD to vary over time (time-varying effect)[8]. Time since index date will be used as the underlying time scale. Standardized cumulative incidence and its differences of arrhythmia will be estimated. We will report the cumulative incidence difference at 1 year, 5 years, 10 years, and 25 years after index date. In the population matched cohort, we will condition the analyses on the matching variables (birth year, sex, county of residence, and calendar year) in model 1, and additionally adjust for country of birth, educational attainment, number of healthcare visits, ischemic heart disease, heart failure, stroke, hypertension, diabetes, obesity, dyslipidemia, chronic kidney disease, and COPD in model 2.

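### The planned incidence rate difference has no age standardisation, so it understates an excess of arrhythmia if IBD patients leave follow-up sooner than their matched comparators

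*SAP*

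**What the plan says.** The SAP, STATISTICAL ANALYSES, opens with the rate measures: "We will report incidence rate (IR) and IR difference, together with 95% confidence intervals (CIs) for all outcomes". It attaches no age split, weighting, model or standard population to them.

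The same section does standardise another absolute measure: "Standardized cumulative incidence and its differences of arrhythmia will be estimated". It gives the reporting times as well: "We will report the cumulative incidence difference at 1 year, 5 years, 10 years, and 25 years after index date".

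Use of the matching variables is described with the regression models: "we will condition the analyses on the matching variables (birth year, sex, county of residence, and calendar year) in model 1".

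The section on reference individuals sets the matching: "we will randomly select up to five reference individuals from the Total Population Register (matched by birth year, sex, county of residence, and calendar year". It is done once, at the index date.

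The follow-up section lists the exits: "Follow-up will start at index date until incident diagnosis of arrhythmias, emigration, death, or December 31, 2019, whichever occurs first". Comparators have one more: "Reference individuals or IBD-free full siblings will also be censored when receiving a diagnosis of IBD during follow-up". The earliest index period in the subgroup section starts in 1969, so follow-up can last about 50 years.

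**The concern.** A pooled incidence rate is an average of age-specific rates, weighted by where the person-time falls. Matching on birth year and calendar year makes the two groups equally old at the index date. It does not keep their person-time equally old afterwards if one group leaves faster. Arrhythmia and death both become more common with age. If IBD patients die sooner, the person-time they lose is mostly at old ages, where arrhythmia rates are highest. The event itself ends follow-up too, so a true excess of arrhythmia has a smaller effect of the same kind.

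The crude difference then mixes the excess associated with IBD with a difference in attained age. Its confidence interval covers sampling error only. A reader could see a hazard ratio clearly above 1 beside a rate difference near zero and have no way to tell why.

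**Working it through.** The SAP states no incidence rate, rate difference or mortality figure, so there is no planned figure to reproduce. The check asks how far a crude difference can move from an age-standardised one.

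**Decomposition.** Let w1(a) and w0(a) be the shares of IBD and reference person-time at attained age a, and r1(a) and r0(a) the arrhythmia rates. Then

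crude difference = Σ w1·r1 − Σ w0·r0 = Σ w0·(r1 − r0) + Σ (w1 − w0)·r1.

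The first term is the difference standardised to reference person-time. The second is the age-mix term, which is negative when IBD person-time is younger and rates rise with age. With IBD weights the split is Σ w1·(r1 − r0) + Σ (w1 − w0)·r0.

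**Inputs from the SAP.** Equal age and calendar year at index; exit at arrhythmia, death or end of 2019; follow-up of up to about 50 years.

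**Assumed inputs, none from the SAP.** Age at index is a mixture centred on 30 and 60 years. Administrative follow-up is spread evenly from about 2 to 50 years. Mortality rises 9.5% per year of age. The arrhythmia hazard rises 9.5% per year of age and is capped at 8% per year. The true hazard ratio is 1.15. Emigration and comparator censoring at IBD diagnosis are left out.

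**Result by numerical integration**, per 10,000 person-years, reference rate 48.8, standardised in 10-year attained-age bands to reference person-time:

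| Mortality ratio | Crude difference | Standardised | Age-mix term | Shortfall |
| --- | --- | --- | --- | --- |
| 1.0 | 6.10 | 7.23 | −1.13 | 1 − 6.10/7.23 = 16% |
| 1.2 | 3.15 | 7.00 | −3.85 | 1 − 3.15/7.00 = 55% |
| 1.3 | 1.84 | 6.89 | −5.05 | 1 − 1.84/6.89 = 73% |
| 1.5 | −0.52 | 6.68 | −7.20 | over 100% |

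The true excess on reference person-time is 0.15 × 48.8 = 7.32. Standardisation recovers 7.23/7.32 = 99% of it at equal mortality and 6.68/7.32 = 91% at ratio 1.5. The remainder is consistent with age differences left within 10-year bands, which favours narrower ones.

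**Two further calculations on other assumed hazards**, hazard ratio 1.15, also per 10,000 person-years:

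- An integration gives crude against standardised differences of 8.2 and 9.3 at equal mortality (shortfall 12%), 4.8 and 8.8 at ratio 1.2 (45%), and 1.8 and 8.3 at ratio 1.4 (78%).
- A simulation standardised to IBD person-time in 5-year bands gives, at mortality ratio 1.4, crude rates of 70.7 (reference) and 71.5 (IBD), a difference of 0.8. The standardised reference rate is 62.6, so the standardised difference is 71.5 − 62.6 = 8.9 and the age-mix term is 62.6 − 70.7 = −8.1; 8.9 − 8.1 = 0.8. At mortality ratio 1.2 the figures are 4.8 and 9.9 (52%).

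**With no true effect** the crude difference is −6.1 at mortality ratio 1.5 (first integration) and −5.8 at ratio 1.4 (second): a spurious deficit made up of the age-mix term alone.

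**What changes the size** (first integration, crude against standardised):

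- Hazard ratio, at mortality ratio 1.2: 1.22 and 4.60 for a hazard ratio of 1.10 (73% lost); 5.06 and 9.40 for 1.20 (46% lost).
- Weaker age gradient, 5% per year, hazard ratio 1.15: 5.25 and 5.49 at equal mortality (4% lost); 3.99 and 5.42 at ratio 1.2 (26%); 2.44 and 5.31 at ratio 1.5 (54%).
- Length of follow-up, hazard ratio 1.15 and mortality ratio 1.5, with the true excess taken as 0.15 × the reference rate: 2.2 against 4.6 when everyone has up to 10 years, 0.3 against 6.3 with 25 years, −2.4 against 9.9 with 50 years.
- Index age 18 to under 40, hazard ratio 1.15 and mortality ratio 1.5: 1.6 against 2.8.

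**The case against.** The strongest reply has four parts.

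First, the SAP never calls the rates crude. That is an inference from silence. It stands as the plain reading, because the same section attaches the word for standardisation only to the cumulative incidence and ties the matching variables to the models. If standardised rates were intended, the SAP still has to say so.

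Second, the measures that carry the inference are protected. The models condition on birth year and calendar year and use time since index, so people compared at a given time are of nearly the same age. A standardised absolute measure is also planned at four time points. This is right and limits the point: the hazard ratios and cumulative incidence differences do not rest on the crude rates. It does not repair the rate difference, which is a separate estimate promised with its own interval.

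Third, the near-zero result needs excess mortality in IBD, a modest hazard ratio and a steep age gradient, and the SAP gives none of them. This also stands. At equal mortality the loss is modest.

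Fourth, a crude rate is a valid description of events per observed person-year. It is, provided it is labelled so and not read as the excess due to IBD.

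A reader might infer that the rate difference is biased towards or past zero for every outcome and subgroup. The documents do not support that. The subgroup section promises the risk of overall arrhythmia and names no rate difference, and the calculations model one generic arrhythmia hazard, not the four secondary outcomes.

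**Conclusion.** The point holds as an improvement to one reported measure. As written, the incidence rate difference is unadjusted, and matching at the index date does not keep attained age balanced over decades. With a true hazard ratio of 1.15 and a steep age gradient, the crude difference falls short by about 10-15% at equal mortality and by about 45-55% at a mortality ratio of 1.2, and it is close to zero or slightly negative at ratios of about 1.4-1.5. With a 5% per year gradient the shortfalls are 4%, 26% and 54% at ratios of 1.0, 1.2 and 1.5. The direction depends on IBD patients leaving follow-up sooner through death or the event, and every magnitude rests on assumed rates. The tempting stronger conclusion, that the study's main association is distorted, does not follow, because the hazard models do not use the crude rates.

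**What to change.** In STATISTICAL ANALYSES, state that follow-up will be split by attained age, for example in 5-year bands. Report the incidence rate difference standardised to the attained-age and sex distribution of the IBD person-time, by direct standardisation or a Poisson model, with its 95% confidence interval. Keep the crude rates but label them as descriptive. State that the absolute effect is read from the standardised rate difference and the standardised cumulative incidence difference.

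The cost is SAP wording, one person-time split and one more set of rates to report. No new data are needed, and the planned hazard models do not change.

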**Subgroup and sensitivity analyses**

We will calculate the risk of overall arrhythmia by sex, age at index date (<18, 18-<40, 40-<60, and ≥60), calendar period at index date (1969-1989, 1990-1999, 2000-2009, and 2010-2019), educational attainment (0-9 y, 10-12 y, ≥13 y, and “missing”), and number of healthcare visits (0, 1, 2-3, and ≥4). We will also explore the associations by location for CD, by extent for UC according to the Montreal classification, and by occurrence of primary sclerosing cholangitis or other extraintestinal manifestations (see below **Table 2** for ICD codes) [3].

Several sensitivity analyses will be conducted. **First,** due to lack of detailed data on smoking, we will restrict the analysis to those without COPD (a proxy for heavy smoking) before index date. **Second,** we will restrict the analysis to individuals with data available on educational attainment. **Third,** given that the Prescribed Drug Register is available since July 2005, we will restrict the analysis to individuals with index date later than 1 January 2006 and apply the statistical models further adjusting for the above mentioned cardiovascular related medications. **Fourth,** we will repeat the main analysis after excluding individuals with incident arrhythmias recorded within 1 year or within 3 years of follow-up after index date. **Fifth,** we will compare patients with IBD with their IBD-free full siblings after conditioning on family identifier and adjusting for birth year, sex, county of residence, calendar year, and all above mentioned covariates.

Data analyses will be performed using SAS version 9.4 (SAS Institute Inc, Cary, NC), Stata (version 16.1; Stata Corp LP, College Station, TX), and R version 3.6.0. A two-sided *P* ≤ 0.05 will be considered statistically significant.

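### Cumulative incidence to 25 years is planned with no model for death, so the named arrhythmia models imply a net risk that overstates each group's absolute risk and biases the difference in a direction set by relative mortality

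*SAP*

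**What the plan says.** On follow-up, the SAP states: "Follow-up will start at index date until incident diagnosis of arrhythmias, emigration, death, or December 31, 2019, whichever occurs first" (Follow-up and ascertainment of outcome). Death stands in the same list as emigration and the administrative end date and has no status of its own. The sentence after it describes comparators who later receive an IBD diagnosis as likewise censored.

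On the model, Statistical Analyses names flexible parametric survival models for incident arrhythmia, with an IBD effect that may vary over time since the index date.

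On absolute risk, the same section says "Standardized cumulative incidence and its differences of arrhythmia will be estimated", and then "We will report the cumulative incidence difference at 1 year, 5 years, 10 years, and 25 years after index date".

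Competing risks, a cause-specific cumulative incidence function and a model for death are mentioned nowhere: not in the main analysis, not in the subgroup and sensitivity analyses, and not among the analyses added after external review. How the cumulative incidence is to be computed from the fitted model is not stated. The cohort covers all ages, and the subgroup section has a stratum of 60 years and over.

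**The concern.** A survival model for arrhythmia in which death is a censoring event estimates the arrhythmia hazard among people still alive and free of arrhythmia. Turning that hazard alone into a risk, and averaging over covariates, gives 1−S. This is the proportion who would have an arrhythmia by a given time if death were removed and the hazard stayed the same. A cumulative incidence in the ordinary sense, the proportion who actually receive the diagnosis, also needs the hazard of death, and nothing in the plan supplies it.

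At short horizons the two quantities nearly coincide. At 10 and 25 years, in a cohort that includes people aged 60 and over, many deaths will come before any arrhythmia. Published absolute risks could then be materially too high. The difference between IBD and reference would mix a real difference in arrhythmia with the omitted effect of any difference in mortality.

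**Working it through.** **Plan's own figure.** None. The SAP gives no arrhythmia rate, death rate, event count or relative mortality. Every rate below is an assumption, and the death HR (IBD versus reference) is varied to show the range. Only the horizons (1, 5, 10 and 25 years) come from the SAP.

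**Formulas.** With constant hazards a (arrhythmia) and d (death):

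- Net risk, death censored: 1 − exp(−aT)
- Cumulative incidence with death competing: a/(a+d) × [1 − exp(−(a+d)T)]

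**Direction for each group.** For any hazards, the net risk is the integral of a·S_a, and the cumulative incidence is the integral of a·S_a·S_d, where S_a and S_d are the survival functions for arrhythmia and death. Since S_d is at most 1, the net risk is never smaller. The gap, the integral of a·S_a·(1 − S_d), can only grow with time.

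**Scenario A, mixed ages (assumed).** Reference a = 0.006, d = 0.010 per year; arrhythmia HR 1.15, so a = 0.0069 in IBD; T = 25.

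- Net, reference: 1 − exp(−0.15) = 13.93%
- Net, IBD: 1 − exp(−0.1725) = 15.84%; difference 1.91 points
- Competing, reference: 0.006/0.016 × [1 − exp(−0.40)] = 12.36%
- Competing, IBD at death HR 1.3: 0.0069/0.0199 × [1 − exp(−0.4975)] = 13.59%; difference 1.23 points

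**Scenario B, older ages (assumed).** Reference a = 0.025, d = 0.04; arrhythmia HR 1.15, so a = 0.02875 in IBD; T = 25.

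- Net, reference: 1 − exp(−0.625) = 46.47%
- Net, IBD: 1 − exp(−0.71875) = 51.26%; difference 4.79 points
- Competing, reference: 0.025/0.065 × [1 − exp(−1.625)] = 30.89%
- Competing, IBD at death HR 1.3: 0.02875/0.08075 × [1 − exp(−2.01875)] = 30.87%; difference about 0

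**25-year difference in percentage points, by assumed death HR**

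| Scenario | Net (1−S) | Competing, death HR 0.8 | Competing, death HR 1.0 | Competing, death HR 1.3 |
|---|---|---|---|---|
| A: 0.6%/y, 1%/y | 1.91 | 2.04 | 1.71 | 1.23 |
| B: 2.5%/y, 4%/y | 4.79 | 6.07 | 3.43 | −0.01 |

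**Other horizons.** At 10 years in scenario B with death HR 1.3, the difference is 2.87 net against 1.34 with death competing, so the issue is not confined to 25 years. At 1 year it is 0.37 against 0.34 in B, and 0.09 against 0.09 in A.

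**Other assumed rates (arrhythmia HR 1.2, 25 years).**

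- Arrhythmia 20 and death 40 per 1000 person-years: the difference is 5.77 net, against 4.03, 1.93 and −0.82 at death HR 1.0, 1.2 and 1.5. The sign can change.
- Arrhythmia 8 and death 12 per 1000: 3.21 net, against 2.81 at death HR 1.0 and 3.32 at 0.8. Net and competing differences are equal near a death HR of 0.84.
- Very high rates, 80 and 40 per 1000, with equal mortality: 4.46 net against 4.88. Here the net difference is too small although mortality is equal.
- Hazards rising 9% per year from 40 and 60 per 1000, with equal mortality: 1.22 net against 4.45, again too small.

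**The case against.** The strongest reply is that the SAP names the right quantity and merely omits the estimator. Neither 1−S nor a cause-specific function is written down, and a competing-risk analysis would also stop follow-up at death, so the list of end-of-follow-up events settles nothing by itself. That stands in part: a reader might infer that the SAP commits to 1−S, and it does not say so. But death is grouped with emigration and the end date, and arrhythmia is the only event for which a model is named. That the SAP speaks of models in the plural does not help, because none is for death. The absolute risk obtainable from what is named is 1−S.

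Three further readings are tempting and go beyond the document.

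- **That the difference will be overstated.** This is not guaranteed. The SAP gives no relative mortality. With a death HR of 0.8, or with very high hazards, the net difference is too small.
- **That the excess in people aged 60 and over vanishes at 25 years.** That result rests on an assumed death HR of 1.3; with equal mortality the same rates leave 3.4 points. Nor does the SAP expressly commit to a 25-year difference within that stratum: the horizons are set without reference to strata, and the subgroup section speaks only of risk by age.
- **That the risk difference is the headline result and the study's conclusions fall with it.** The SAP does not rank it so. It also plans incidence rates, rate differences and hazard ratios, none of which is invalidated by censoring at death, and its hypothesis of increased risk can be examined through them.

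**Conclusion.** The concern holds in limited form. As the plan stands, the named models imply a net risk where a cumulative incidence is promised.

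- If 1−S is reported and read as actual risk, overstatement of each group's absolute risk is certain. The size depends on rates: at 25 years the reference risk is 13.9% against 12.4% under the mixed-age assumptions, and 46.5% against 30.9% under the older-age assumptions.
- For the IBD-reference difference, overstatement is likely if mortality in IBD is equal or higher. Understatement is possible if it is lower or if hazards are very high. Size and sign therefore cannot be settled from the SAP.
- At 1 year the effect is negligible.

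All figures rest on assumed rates, and those in this verdict on constant hazards; they illustrate scale and are not predictions for this cohort. This should be fixed because it affects reported 10- and 25-year results, but it does not undermine the relative measures.

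**What to change.** In Statistical Analyses:

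1. State that death is a competing event for the cumulative incidence.
2. Add a second flexible parametric model, for death without prior arrhythmia.
3. Combine the two cause-specific hazards into standardized cause-specific cumulative incidence functions. Report these and their differences at 1, 5, 10 and 25 years, with an Aalen-Johansen estimate as a check.
4. Keep the cause-specific HR for arrhythmia as the relative measure.
5. Label any 1−S result that is still shown as a net risk. Labelling alone is the minimum correction and needs no second model, but it leaves the actual risk unreported.

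The cost is SAP wording and one extra model on data already held, since death already ends follow-up. The stated absolute risks become smaller, and the differences may move either way. The modification history expected the analyses to be run by January 2023, so a change made now belongs with the analyses that the SAP already lists as not prespecified.
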